## 3) Several sub studies are planned:

1. Due to the chosen randomization procedure it will be possible to perform analyses on the randomized intervention trial on the subgroups listed in section 8: age, gender, diabetes mellitus, heart failure, time from last myocardial infarction or invasive cardiological procedure. Degree of depression is listed among the main purpose, section 2.
2. Comparison of the chosen PPS measure with another and established algometer.

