### 5.2 Inclusion criteria:

- Implemented cardiac rehabilitation program at Gentofte or Herlev Hospital minimum 6 months ago.
- Documented ischemic heart disease that qualified for a heart rehabilitation program.
- Use of aspirin, cholesterol-lowering and antihypertensive medication after Danish cardiac guidelines.
- Younger than 75 years at the time of inclusion.
- Elevated level of stress, defined as PPS  $\geq$  60.

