#### *6.3.4 Health economics (cost / benefit) analysis*

Data from the last 12 months prior to the inclusion date will be used as baseline variables. This is only executed if the primary and secondary effect objectives meet the criteria for success (see paragraph 12). Data will be collected for the following services:

1. Number of visits to the practitioner (for heart problems)
2. Number of visits to a cardiologist (specialist)
3. Number of hospital visits (outpatient)
4. Number of inpatient days in a hospital

5. Use of invasive procedures (PCI and/or CABG)
6. Use of cardiovascular medicine
7. Number of sick days due to heart disease (if the person is working)

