## **7. Practical course (including flowchart)**

Using databases of cardiac rehabilitation patients from Gentofte and Herlev Hospital respectively approximately 600 patients with complete cardiac rehabilitation course > 6 months ago, to ensure a steady state in regard to the efficacy of the given cardiac rehabilitation, are identified. The patients are invited by letter to participate in the study.

It is expected that about 450 will accept. These are convened to an examination at Herlev Hospital Medical Department O.

All patients sign the consent form and go through the physiological preliminary examination.

Patients with PPS < 60 are ended immediately, and a subset of the first 50 patients with PPS < 45 are invited to a measuring of their body composition.

Since it is expected that 2/3 of patients have an elevated PPS measure ( $\geq 60$ ), 300 patients with PPS  $\geq 60$  are randomized to either an active or control group with 150 in each:

**Control group:** Continue their own efforts in extension of the already given cardiac rehabilitation and receive a textbook on general stress management (REHAB + CARE).

**Active group:** the same plus the Ull treatment program (REHAB + ULL).

All included patients will at baseline be offered an additional measurement of body composition.

Intervention period: 3 months.

Both the control and active group continue with the given medical treatment. If there is a change in heart condition including possible side effects of medication, the medication is adjusted according to the procedures in the rehabilitation programs at the hospital the patient is assigned to (Gentofte or Herlev Hospital). If possible, the medication should remain stable during the 3 months of the observation. The patient and the patient's own doctor are informed that the aim of the study is that any adjustment of cardiovascular medicine happen after contact with the project nurse (perhaps through a telephone hot-line).

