**Control/Active group:**

1. Control group: receive a book about general stress management
2. Active group: receive in addition to the above mentioned:

Instruction in self-measurement of PPS by a PPS instructor at home. The patient is instructed in PPS measurement, nerve stimulation and the use of the web platform in order to be able to enter their own measurements. They are not instructed in stress management. There is a 45 minute home visit in the beginning plus two visits after one and two months respectively for additional technical instruction if the PPS measure is  $\geq 60$ . In addition there are 5 telephone dialogues á 15 minutes solely for technical instruction after 1, 3, 5, 6 and 10 weeks respectively. The patients receive an Ull meter, a written user's manual and an instructional DVD.

The patients record their PPS measurements either on the web platform ([www.songheart.org](http://www.songheart.org)) or on paper at least once a week

If their PPS records show a  $PPS \geq 60$  for 7 consecutive morning measurements, the patient is contacted regarding the need for additional technical instruction.

After three months of participation in the project all patients (both groups) are called to a repetition of the baseline visit at Herlev Hospital. Those who at baseline opted to have made body composition will have the same offer again if, at the physiological examination, they have lost 3 kg or more.

The two examinations at Herlev are conducted by the same blinded nurse at baseline and the 3 month follow-up respectively.

If the success criteria for the study are met, the subsequent analysis are carried out after the 12 month observation:

Use of health services over the last 12 months before the start of the study compared to the 12 months after commencement of participation.

The prevalence of clinical events. Here a Kaplan-Meier plot analysis will be used.

The Minimal Important Difference (MID) between the active and control group is set at a 10 % improvement in the active group versus the control group.

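### The 12-month look-back for health-service use is longer than the 6 months since rehabilitation that eligibility guarantees, so a before-versus-after fall is not evidence of effect and the change score can lose precision

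*Protocol*

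**What the plan says.** - **Look-back.** Section 6.3.4 states: "Data from the last 12 months prior to the inclusion date will be used as baseline variables". The services counted include outpatient hospital visits, inpatient days, PCI/CABG, cardiovascular medicine and sick days.
- **Comparison.** Section 7, under the control/active group text, sets it out as "Use of health services over the last 12 months before the start of the study compared to the 12 months after commencement of participation". The sentence names no arm. Shortly after it, the minimal important difference is "set at a 10 % improvement in the active group versus the control group".
- **Eligibility.** Section 5.2 requires "Implemented cardiac rehabilitation program at Gentofte or Herlev Hospital minimum 6 months ago". Section 7 gives the reason: "to ensure a steady state in regard to the efficacy of the given cardiac rehabilitation". No upper limit on time since rehabilitation is stated.
- **Analysis.** Section 11.2 compares the changes in the active and control groups. It names baseline MDI as covariate and makes health economics the second priority hypothesis in the closed test procedure. Section 11.3 compares active with control treatment.
- **Recency.** Section 3, item 3, names "time from last myocardial infarction or invasive cardiological procedure" among subgroups said to be listed in section 8. Section 8 lists age, gender, heart failure, diabetes and MDI only. Section 11.5 has time since last MI or procedure as a subgroup, cut at 2 years.

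**The concern.** The protocol's own argument is that patients need 6 months after rehabilitation to be in a steady state. A 12-month look-back reaches past that point. Months 7 to 12 before inclusion may contain the rehabilitation itself and, depending on how long it lasted, the admission or procedure that led to it. These generate exactly the services being counted.

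Two consequences follow. First, use can fall from the year before to the year after in both arms even if the programme is inert, so the section 7 sentence, followed literally, cannot show an effect. Second, a change score carries the extra look-back use as noise, because an old event says little about use in the year after inclusion. This can weaken the test of the second priority hypothesis.

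**Working it through.** **1. Overlap of the windows.** The look-back is 12 months (sections 6.3.4 and 7) and the guaranteed time since rehabilitation is 6 months (sections 5.2 and 7). The unprotected part is 12 − 6 = 6 months. It matters only for patients whose rehabilitation ended 6 to 12 months before inclusion.

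The protocol gives no rate, SD or sample size for health-service use, so there is no planned figure to reproduce. Everything below rests on assumed inputs.

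**2. Fall within an arm with no treatment effect.** Let s be the share of patients affected and m their extra look-back use, as a multiple of a normal year. The mean before is 1 + s·m and the mean after is 1, so the fall is 1 − 1/(1 + s·m).

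| s | m = 0.5 | m = 1 | m = 3 |
|---|---|---|---|
| 0 | 0% | 0% | 0% |
| 10% | 4.8% | 9.1% | 23.1% |
| 25% | 11.1% | 20.0% | 42.9% |
| 50% | 20.0% | 33.3% | 60.0% |

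**3. False-positive rates, no treatment effect.** Simulation with 150 per arm (section 7). Assumed: steady use with mean 5 contacts a year, gamma-distributed between patients (shape 1, variance 25), and Poisson counts.

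| s, m | Within-arm before-after test | Between-arm test of changes |
|---|---|---|
| 0, – | 4.9% | 4.4% |
| 10%, 1 | 41% | 5.1% |
| 25%, 1 | 97% | 5.1% |
| 25%, 3 | 100% | 5.4% |

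The mean between-arm difference in changes was about 0 in every scenario.

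**4. Precision of the between-arm comparison.** Under the same model:
- Var(post) = 25 + 5 = 30
- Cov(pre, post) = 25
- Var(pre) = 30 + s(1 − s)(5m)² + 5sm

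The SE of an arm difference is √(2V/150), where V is:
- follow-up alone: 30
- change score: 30 + Var(pre) − 50
- follow-up adjusted for look-back use: 30 − 25²/Var(pre)

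| s, m | Var(pre) | Change score: V, SE | Follow-up alone: SE | Adjusted follow-up: V, SE |
|---|---|---|---|---|
| 0, – | 30 | 10, 0.37 | 0.63 | 9.17, 0.35 |
| 10%, 1 | 32.75 | 12.75, 0.41 | 0.63 | 10.92, 0.38 |
| 25%, 1 | 35.94 | 15.94, 0.46 | 0.63 | 12.61, 0.41 |
| 25%, 3 | 75.94 | 55.94, 0.86 | 0.63 | 21.77, 0.54 |

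The simulated SDs agree: 0.37, 0.42, 0.46 and 0.87 for the change score and about 0.63 for follow-up alone. With moderate contamination the change score loses some precision (variance 15.94/10 = 1.6 times the clean case) but still beats follow-up alone. Only in the heaviest row is it worse than ignoring the baseline. Adjustment has the smallest SE in every row.

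**5. Chance imbalance in recency.** If 20% of patients are affected (assumed), the SE of the arm difference in that share is √(2 × 0.2 × 0.8/150) = 4.6 percentage points. A 5-point imbalance is 5/4.6 ≈ 1.1 SE, and one at least that large in either direction arises in about 28% of trials.

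**The case against.** A reader might infer that the plan would credit the programme with a saving that is only the natural course after a cardiac event. The documents do not support that. The minimal important difference that follows the quoted sentence is active versus control, section 11.2 compares changes between arms, section 11.3 compares the treatments, and section 6.3.4 calls the look-back data baseline variables. Nowhere is a within-arm fall said to count as effect. The expected fall is the same in both randomised arms, so the contrast is unbiased. This stands.

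A reader might also infer that the arms will be unbalanced on recency because it is not a minimisation factor. They are balanced in expectation, and a 5-point imbalance is ordinary sampling error already reflected in the standard error. This stands too.

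Nor can one say that use will fall, or that the follow-up year is free of such contacts. The affected share is unstated and could be small. The Summary and section 9.2.1 say patients continue in rehabilitation, and new events can occur.

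Finally, the outcome is tertiary in section 6.3, runs only if the success criteria are met, and comes after MDI in the closed test. That lowers the severity. It does not remove the mismatch between the windows, the literal wording of the section 7 sentence, or the possible loss of precision.

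**Conclusion.** The point holds in limited form. Up to 6 of the 12 look-back months lie outside the period the protocol itself regards as steady. The before-versus-after comparison worded in section 7 therefore cannot serve as evidence of effect. The between-arm comparison of changes is valid but can be less precise than it need be. The loss is modest under moderate assumed contamination (SE 0.37 to 0.46) and large only under heavy contamination (0.86). All these sizes depend on an assumed affected share, extra use and contact rate, none of which the protocol gives.

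Separately, section 3 says that time since last MI or procedure is listed in section 8, and it is not.

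Severity is minor to moderate: a conditional, tertiary outcome that nevertheless holds second place in the closed test procedure.

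**What to change.** In sections 6.3.4 and 7:

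- State that the test is the between-arm comparison of use in the 12 months after inclusion.
- Adjust for look-back use as a covariate instead of analysing a change score. Also adjust for time since rehabilitation or last MI/procedure, preferably continuous or with a cut at 12 months. The 2-year cut in section 11.5 is too coarse, because it puts a patient at 7 months with one at 23.
- Flag or exclude rehabilitation and index-event contacts in the look-back.
- State that the within-arm before-after change is descriptive and is not interpreted as an effect.

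Reconcile section 3, item 3, with the factor list in section 8.

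Shortening the look-back to 6 months is an alternative, but a trade-off: it makes rare items such as procedures and inpatient days sparser and gives up matched annual windows. Keeping 12 months with adjustment and flagging avoids this.

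The cost is mainly wording, plus slightly more analysis work to date and flag the contacts. The before-after saving can no longer be quoted.

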## 7.1 Flowchart:

| Visit (number)                             | 1      | 2          | 3         | 4                                  |
|--------------------------------------------|--------|------------|-----------|------------------------------------|
| Physical location                          | Herlev | Home visit | Herlev    | Data collection via public records |
| Months                                     | 0      | 0          | 3         | 12                                 |
| Window for visits                          |        | +/-7 days  | +/-7 days |                                    |
| Informed consent                           | X      |            |           |                                    |
| Questionnaires completed                   | X      |            | X         |                                    |
| Inclusion/exclusion                        | X      |            |           |                                    |
| Blood pressure, pulse, PPS and HRV test    | X      |            | X         |                                    |
| Blood sample                               | X      |            | X         |                                    |
| Assessment of medication                   | X      |            | X         |                                    |
| Randomization                              | X      |            |           |                                    |
| Registration of clinical events            | X      |            |           | X                                  |
| Consumption of healthcare services         | X      |            |           | X                                  |
| Implementation of joint treatment          | X      |            |           |                                    |
| Implementation of active treatment         |        | X          |           |                                    |
| Measurement of body composition (subgroup) | X      |            | X         |                                    |

CONSORT Flow Chart for the SongHeart study

[figure not shown]

## 8. Randomization procedure

The treatment is assigned randomized and with an equal number of patients in the control group and for active intervention. An independent research company electronically conducts the practical randomization ([www.larix.dk](http://www.larix.dk)).

The treatment is allocated by a minimization procedure with built-in randomness (Pocock and Simon, 1975). The minimizing will ensure an approximate balance in the number of patients in both treatment groups with respectively low and high values of the baseline parameters taken into account in the procedure. Pocock and Simon's minimization method (Pocock and Simon, 1975) will be used with a randomness parameter of 0.8. The following baseline parameters will be included:

- Age ( $< 65$ ,  $\geq 65$  years)

- Gender (male, Female)

- Heart failure (Yes, No)

- Diabetes (Yes, No)

- MDI (score  $<15$ ,  $\geq 15$ )

The result of the randomization is blinded to the investigating nurses and doctors and other who are hired to participate in the study, including the statisticians who analyze the data in relation to the main scientific article. The people conducting the training of the active group as well as patients are excluded from blinding.

## 9. Methods

### 9.1 Stress measurement:

An Ull Meter is used, which is an instrument developed to measure the sensibility/activity in the polymodal nervous system corresponding to the most painful point on the sternum between costa 3-5. The point is identified by finger pressure. First the patient learns his/hers pain threshold as the instructor applies a gradually increasing pressure on the tibia with the instrument and the patient says stop when the threshold of pain/discomfort is reached. The procedure is then repeated on the most tender place on the sternum while the patient himself

applies the pressure and stops when the pain threshold is reached. The instrument then displays a number on a scale from 30 to 100, where an increased sensibility is accompanied by an increasing number, PPS; meaning that a high PPS measure reflects a high level of stress (high sensitivity) (Ballegaard et al., 2009).

The Ull Meter has the following special features:

- Hidden measurement value until the measurement is completed.
- A calculation of the sensitivity to a tenderness score on a logarithmic scale similar to the decibel scale used to estimate the limit values of sound pressure in connection with a hearing test.
- An alarm that is activated by a pressure before the occurrence of any injury.
- A special foot pad that prevents irritation of the skin to ensure that it is the pressure sensitivity of the bone that is measured and not the skin's sensitivity.

## **9.2. Treatment modalities:**

### *9.2.1 Current cardiac rehabilitation:*

All patients have been through and take part in the cardiac rehabilitation as defined by the respective cardiology departments and according to public health regulations (The National Board of Health, 2004; The network group of "heart rehabilitation", 2004)

### *9.2.2 The Ull Care program:*

The basic elements of the intervention are as follows:

1. A self-care part.
2. A professional instruction in the PPS measurement, cognitive reflection in relation to the measure and nerve stimulation.
3. Continuous recording of the participants' PPS measurements through a Web journal.

The self-care based intervention program is a stress management program based on the use of the PPS measure as a biofeedback marker of stress. The most important effort is the daily

self-care in the form of PPS measuring, cognitive reflection and nerve stimulation, which is linked to professional technical help depending on need.

### *The elements of the self-care program*

An individual start-up of a 45-minutes face-to-face consultation at home with an Ull Care instructor who explains the use of the instrument, the interpretation of the PPS measurement, nerve stimulation and the web platform.

A personal Ull Meter instrument.

A personal web journal for track recording of the participant's PPS measure's development (patients without internet access will receive printed registration sheets).

A booklet that describes the self-care program in details.

Two additional face-to-face meetings with additional technical instruction should the PPS measure remain  $\geq 60$  after 1 and 2 months respectively.

5 x 15 minutes of telephone consultations after 1, 3, 5, 6 and 10 weeks respectively.

Only the following four subjects may be discussed: the PPS measure, interpretation of the measurements, nerve stimulation and the use of the web journal. This is to ensure a correct use of the Ull Meter instrument and a correct management of the nerve stimulation technique.

Online assessment of the participant's PPS measurements. This assessment is made automatically on the website. If the morning PPS measure has been  $\geq 60$  for more than seven days in a row, the participant is offered additional technical support.

### *The daily steps of the self-care program*

Four elements constitute the daily self-care system: measuring, cognitive reflection, action and control.

**Measuring:** PPS is measured twice a day as a fully private measure and is entered in a personal web journal, so that the person can track his/hers own development, while at the same time there is a regular external professional control.

**Reflection:** Cognitive reflection as a reaction to the actual PPS measure and its development.

**Action:** Nerve stimulation on selected acupuncture points corresponding to the

instruction. Possible further own efforts are as mentioned in the book on general stress management given to all participants (both the active and control group). The PPS measure is used as a personal feedback marker of stress, taking into account the effect of the participant's chosen effort.

**Control:** Measure the effect of any action/inaction at any time.

This four-step procedure should be done at least twice a day (morning and evening) to be preventive; it is recommended to perform the procedure morning and evening in order to promote the construction of a conditioned reflex. This reflex (i) facilitates the habit and (ii) improves the effect of the action, which is important for ad-hoc use, should the participant want to reduce his/hers level of stress acutely or if he/she experience chest pain. It is important the program is not perceived as a chore, which is emphasized to the patient.

#### *The specific therapeutic elements of the program:*

Biofeedback measuring of stress using the PPS measure as the measure of stress and to what extent the patient's heart is affected by stress followed by:

- Sensory nerve stimulation (acupressure/shiatsu massage)

The patients are instructed to perform the preventive nerve stimulation twice a day plus ad hoc when they urgently want to reduce their stress. Nerve stimulation is done by applying pressure with a finger for one minute – you should feel it, but it should not cause any pain, This is done at the following acupuncture points; on the sternum at the level of the fourth intercostals space (Shanzhong, C.V. 17), and on the back 3,8 cm lateral to the spinal process of the fourth and fifth thoracic vertebra (Jueyinshu and Xinshu, U.B. 14 and 15). Nerve stimulation is done successfully when the patient can observe that the tenderness of the point has been reduced after applying pressure. If this result has not been achieved, the patient is instructed to repeat the treatment. The repetitive nerve stimulation has two primary goals: 1) to restore the nervous system's ability to adapt through the repetitive stimulation of the diffuse pain inhibitory control (DNIC) system (Arendt-Nielsen L and Yarnitsky D, 2010) and 2) to reduce an elevated stress level through the repeated non-painful sensory stimulation of the polymodal nerve cell, causing a

release of the oxytocin hormone (Uvns-Moberg, 1997a). If possible, the spouse or cohabitant will be instructed to perform nerve stimulation on the patient's back, which may independently contribute to stress-relieving effects through a separate oxytocin release caused by the human care (Carter et al., 2007;Grewen et al., 2005;Light et al., 2005;Uvns-Moberg, 1997b). If a spouse or cohabitant is not available, the patient can perform the treatment himself with a ball (the person will receive instructions in the technique).

